### Randomization and Treatment

Eligible patients will be randomly assigned to off-pump CABG or on-pump CABG.
Randomization will be performed after the baseline data, including information
about the target vessels have been entered into a central, Internet-based,
password-protected database with the use of a template.

Treatment assignments will be performed in a blinded manner according to a
blocked randomization scheme with a block size of ten, stratified according to
the participating center. Off-pump CABG must be routinely performed at all
participating centers before the trial is initiated. Participating centers
should nominate individual study surgeons for each surgical technique.

Study surgeons will be required to be established experts in the performance of
either off-pump or on-pump CABG. The average number of CABG surgeries performed
before the study will be between 50-100 off-pump surgeries for the off-pump CABG
surgeons and 250 on-pump surgeries for the on-pump CABG surgeons. It will not be
mandatory for the same surgeon who operates the off-pump CABG cases to also
operate the on-pump CABG cases, but always respecting the established protocols
for each surgical technique.

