**Methods:**

FRAGILE is a two-arm, parallel-group, multicentre, individually randomized
(1:1) controlled trial which will enroll 630 patients with blinded outcome
assessment (at 30 days, 6 months, 1 year, 2 years and 3 years), which aims
to compare adverse cardiac and cerebrovascular events after off-pump
*versus* on-pump CABG in pre-frail and frail patients.
Primary outcomes will be all-cause mortality, acute myocardial infarction,
cardiac arrest with successful resuscitation, low cardiac output
syndrome/cardiogenic shock, stroke, and coronary reintervention. Secondary
outcomes will be major adverse cardiac and cerebrovascular events, operative
time, mechanical ventilation time, hyperdynamic shock, new onset of atrial
fibrillation, renal replacement therapy, reoperation for bleeding,
pneumonia, length of stay in intensive care unit, length of stay in
hospital, number of units of blood transfused, graft patency, rate of
complete revascularization, neurobehavioral outcomes after cardiac surgery,
quality of life after cardiac surgery and costs.

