## METHODS

### Study Design

The FRAGILE study will be a national multicenter RCT to be conducted in 10
Brazilian institutions. The study is already approved by a certified ethics
committee. The study sponsor must be the Brazilian Society of Cardiovascular
Surgery and Zerbini Foundation. Funding will be provided by an unrestricted
grant from São Paulo Research Foundation, which otherwise will not have
any role in the conduct of the study nor in the analysis nor in the reporting of
data. There will be confidentiality agreement regarding data use. This RCT will
be monitored by an independent data and safety monitoring board. All the authors
will be provided revisions and comments. All the authors will be testifying for
the accuracy and completeness of the report, as well as for the fidelity of the
report to the study protocol.

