### Study Population

The inclusion criteria will be: participants aged ≥65 years with
indication of myocardial revascularization with ≥2 criteria of frailty by
Fried Frailty Criteria^[16]^,
not eligible for angioplasty treatment by the heart team approach and those
suitable to undergo either off-pump or on-pump CABG.

There is a dose-response relationship, in relation to the number of fragility
criteria and patient outcomes. The categorization of the fragility variable was
performed after the studies showed that the risk increases gradually over 3
categories (0-1, 2-3, 4-5), with risk of similar events within each category.
Thus, patients who had 2 or 3 criteria were considered as pre-frail, and
patients with 4 or 5 criteria were considered as frail^[21]^.

The exclusion criteria will be: patients with indication of another procedure in
addition to CABG; patients who underwent emergency operation (within 24 hours
after hospital admission); patients who underwent previous cardiac surgery, even
with other approaches than median sternotomy; patients who do not have free,
prior and informed consent to participate in this study.

The baseline characteristics of potentially eligible but excluded patients will
be recorded in a screening log. All patients will be provided written informed
consent.

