### Statistical Analysis

The sample size of the FRAGILE trial was based on the ability to detect a 40%
reduction in the primary outcome in the off-pump group compared with the on-pump
group, assuming an event proportion after on-pump CABG of 20.8% and accepting a
risk of type I and II error of 5% and 20%, respectively, and a crossover rate of
5%^[24]^. Consequently,
at least 630 patients will be enrolled.

All of the data will be analyzed according to intention-to-treat
(*i.e.*, based on treatment allocation). Therefore, we will
report treatment-received analyses according to the intervention actually
received. Baseline characteristics and operative characteristics will be
compared with the use of chi-square test, t-test, or Kruskal-Wallis test, as
appropriate. Dichotomous data will be presented as numbers and percentages.
Continuous data will be presented as mean and standard deviation or median and
interquartile range. The continuity corrected chi-square test will be used for
comparison of the 30-day endpoint. Mantel-Haenszel chi-square tests will be used
to adjust for study-center effects. Treatment effects at 30 days will be
expressed as OR and 95% CI. For the 12-month endpoint, Kaplan-Meier curves will
be constructed, and the study groups will be compared with use of the log-rank
test. HR and 95% CI derived from the Cox proportional hazards model will be
provided for the composite outcome and individual components. All statistical
analyses will be performed with the use of the R-3.1.2 language for handling and
storage of data and performing of statistical calculations.

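### A single published block size of ten within each centre lets anyone who keeps a full centre tally know up to one allocation in six in advance

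*Protocol article*

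**What the plan says.** Randomization and Treatment sets out a "blocked randomization scheme with a block size of ten, stratified according to" participating centre. No other block size is given, and nothing says that the size varies or is kept from sites. The abstract (Methods) gives the ratio and the total, "1:1) controlled trial which will enroll 630 patients with blinded outcome" assessment, and Study Design gives the number of institutions: "The FRAGILE study will be a national multicenter RCT to be conducted in 10".

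The next assignment is concealed. It is issued through a central, password-protected web database once baseline data are in, and "Treatment assignments will be performed in a blinded manner according to a" blocked scheme.

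Past assignments are a different matter. The same section says that centres "should nominate individual study surgeons for each surgical technique", and Surgical Technique describes two plainly different operations. Under Study Population, a patient must be "suitable to undergo either off-pump or on-pump CABG"; who makes that judgement is not stated.

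**The concern.** Concealing the list does not stop a site from working out the next assignment from those already made. In a 1:1 block of known size ten, once five patients have received one technique, every remaining place in that block belongs to the other. Stratification by centre means that each centre runs its own sequence, so a local tally is enough.

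A known slot matters only if entry can be influenced. Here it can: suitability for either technique is a matter of judgement, and emergency operations are excluded, so there will usually be time to defer or decline a patient. The article's own Introduction and Discussion favour off-pump surgery in high-risk and frail patients, which supplies a possible motive. If patients of different risk were steered towards or away from known slots, the arms would differ before surgery.

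**Working it through.** The article gives no predictability figure to reproduce, so the check starts from its design inputs.

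**Inputs.** Block size 10, stratified by centre (Randomization and Treatment); ratio 1:1 and N = 630 (abstract, Methods); 10 centres (Study Design). Assumption: equal recruitment, 630/10 = 63 per centre.

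**Step 1: certain allocations in a complete block.** A block holds five places per arm, so there are C(10,5) = 252 equally likely sequences. Position j is certain when all places from j onward belong to one arm, which has probability 2 × C(j−1, 5)/252.

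| Position | Sequences | Probability certain |
|---|---|---|
| 1–5 | 0 | 0% |
| 6 | 2 | 0.8% |
| 7 | 12 | 4.8% |
| 8 | 42 | 16.7% |
| 9 | 112 | 44.4% |
| 10 | 252 | 100% |

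The sum is 420/252 = 1.667 per block, or 16.7%. This agrees with the closed form 1/(m+1) for a block of 2m: 1/6 with m = 5.

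**Step 2: scale to the trial.** If every block were complete, 630/6 = 105. With 63 per centre, there are six full blocks and three patients of a seventh, and the first three positions are never certain. That gives 6 × 1.667 = 10 per centre and 100 in total: 100/630 = 15.9%.

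**Step 3: best guess.** An observer who always guesses the arm with more places left is right, on average, 5 + 2⁹/252 − 1/2 = 6.53 times in ten (65.3%), against 50% by chance.

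**Step 4: other schemes.** For smaller fixed blocks, the closed form gives 1/3 = 33% (blocks of four) and 1/4 = 25% (blocks of six), both worse than ten. Varied blocks were simulated with 63 patients per centre and 3000 runs. The observer knows the set of sizes and the full history, but not which size is in use.

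| Block sizes | Certain | Best guess correct |
|---|---|---|
| 10 fixed | 15.9% | 64.7% |
| 4/6/8 | 2.2% | 67.6% |
| 4/6/8/10 | 1.2% | 66.7% |
| 6/8/10 | 1.6% | 66.0% |
| 8/10/12 | 1.4% | 64.7% |

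Varying the size removes nearly all certainty. It does not lower the best-guess rate, and including small blocks raises it.

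**Step 5: what steering could do (illustration only).** Assume no treatment effect, and steering in every certain slot (one in six): on-pump slots receive patients at k times the usual risk and off-pump slots patients at 1/k times. The off-pump to on-pump risk ratio is then (5/6 + 1/(6k)) / (5/6 + k/6). For k = 1.25, 1.5 and 2 the spurious relative reduction is 7%, 13% and 21%; for k = 1 it is nil. The design target is a 40% reduction (Statistical Analysis). The values of k are assumptions, and steering the other way would bias the result in the other direction.

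**The case against.** The strongest reply is that one in six is a worst case. It needs someone with influence over enrolment who knows the block size, knows where blocks begin, and keeps a complete tally. The off-pump and on-pump operators need not be the same person, so a single surgeon may see only some of the allocations. That stands: the figure is a ceiling. A centre team could pool what it knows, and the block size is in print, but nothing shows that anyone would count. That past allocations are known at the centre is a safe inference from the two operations, not a statement in the article.

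A reader might also infer that surgeons decide suitability. Study Population does not say so; the only decision-maker it names is the heart team, for ineligibility for angioplasty.

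A reader might further infer that no analysis could reveal the problem. That is too strong. Statistical Analysis compares baseline characteristics between arms, and Study Population keeps a screening log of potentially eligible but excluded patients. These might reveal measured imbalance or selective non-enrolment. They cannot reliably detect or undo selection on unmeasured features, and the only adjustment stated is for centre.

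Finally, ten is a fairly large block, better than a fixed four or six. This is true, and it is a reason not to shrink the block. It does not justify a constant, disclosed size. Nor is this a detail lost in condensing the protocol: the article states the scheme and the size outright.

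**Conclusion.** The concern holds as an avoidable weakness in the allocation scheme. With full knowledge of a centre's history, up to 16.7% of allocations in complete blocks are certain in advance, or about 100 of 630 (15.9%) at 63 patients per centre. The enumeration is exact. The trial-wide count rests on equal recruitment and on a complete tally at every centre.

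The document does not support the stronger conclusion that selection bias has occurred or will occur, and it gives no basis for its size or direction. The 65% best-guess rate is also not an argument for varied blocks, since they leave it where it is or raise it slightly for an observer who knows the set of sizes. The case for change rests on removing certainty, plus whatever withholding the sizes adds, which was not quantified.

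**What to change.** For all allocations still to come, replace the fixed block with block sizes that vary at random within centre. Generate the list centrally and do not disclose the sizes to any site until database lock. Avoid small blocks: a set such as 8, 10 and 12 is preferable to one that goes down to 4. The public text can say that block sizes vary and are withheld, without naming them.

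The cost is a regenerated central list and one sentence. With blocks of 12, the largest possible within-centre imbalance rises from 5 to 6. If no block exceeds ten (for example 6, 8 and 10) it stays at 5, at the price of a slightly higher best-guess rate (66.0% against 64.7%).

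### Surgeons are nominated by technique but the planned tests ignore surgeon; if surgeons are separate and outcomes vary by surgeon, the 95% CI is too narrow and type I error can exceed 5%

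*Protocol article*

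**What the plan says.** Under Randomization and Treatment, patients are allocated in blocks of ten stratified by centre. Centres "should nominate individual study surgeons for each surgical technique". Surgeons must be experts in one technique or the other, with different experience figures for the two groups (50 to 100 off-pump operations; 250 on-pump operations). The section adds that it is not "mandatory for the same surgeon who operates the off-pump CABG cases to also" do the on-pump cases. Overlap is therefore allowed but not required, and no number of surgeons is given.

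Under Statistical Analysis, a continuity-corrected chi-square test is named for "comparison of the 30-day endpoint. Mantel-Haenszel chi-square tests will be used" to adjust for centre. The 30-day effect is reported as an odds ratio with a 95% CI. Surgeon appears neither in these tests nor in the sample size statement. The Discussion part of the Abstract frames the conclusion as whether off-pump surgery is superior to on-pump surgery, which is a statement about the techniques.

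**The concern.** Where a centre uses different surgeons for the two techniques, the contrast between surgeons within that centre is the same as the contrast between treatments. Patients operated on by one surgeon tend to have more alike outcomes, but both named tests treat all patients within a centre and arm as independent. Stratifying by centre removes differences between centres. It cannot remove a difference between two surgeons who work in the same centre in opposite arms.

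The article itself holds that surgeons matter. The Introduction suggests that the conversion rates in earlier trials (12.4%, 7.9% and 5%) may reflect inexperienced surgeons, and the Discussion offers surgeon experience as a reason why two earlier trials differed at one year. A plan that reads other trials this way has reason to check for surgeon variation in its own. What is at stake is that chance differences among a small number of surgeons could be reported as a difference between techniques, with an interval that looks more precise than it is.

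**Working it through.** **Inputs from the article.** 10 centres (Study Design); 1:1 individual randomization (Abstract); "at least 630 patients will be enrolled"; "assuming an event proportion after on-pump CABG of 20.8"%; a 40% "reduction in the primary outcome in the off-pump group compared with the on-pump" group; "risk of type I and II error of 5% and 20%, respectively".

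**Inputs assumed.** Surgeon ICC of 0.005 to 0.03; one, two or four surgeons per arm per centre (k); no surgeon in both arms; equal caseloads. None of these is in the documents.

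**The plan's own figure.** The off-pump proportion is 0.208 × 0.6 = 0.1248. The two-sided pooled formula at 5% and 80% gives 314 per arm, or 628 in total, which agrees with 630. Power at 315 per arm is 80.2%. The match leaves out the stated 5% crossover, which is a separate matter. The relevant fact here is that 630 leaves no room for surgeon variation.

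**Analytic check.** Patients per surgeon: m = 630 / (2 × 10 × k), that is 31.5, 15.75 or 7.875. Design effect: DE = 1 + (m − 1) × ICC. A correct interval is √DE times as wide. Actual two-sided error of an uncorrected test: 2 × (1 − Φ(1.96/√DE)).

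Example, k = 1 and ICC 0.01: DE = 1 + 30.5 × 0.01 = 1.305; √DE = 1.142; 1.96/1.142 = 1.716; error = 8.6%.

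| ICC | k = 1: DE, width, error | k = 2: DE, error | k = 4: DE, error |
|---|---|---|---|
| 0.005 | 1.15, ×1.07, 6.8% | 1.07, 5.9% | 1.03, 5.4% |
| 0.01 | 1.31, ×1.14, 8.6% | 1.15, 6.7% | 1.07, 5.8% |
| 0.02 | 1.61, ×1.27, 12.2% | 1.30, 8.5% | 1.14, 6.6% |
| 0.03 | 1.92, ×1.38, 15.7% | 1.44, 10.3% | 1.21, 7.4% |

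**Simulation of the planned tests.** No treatment effect, event risk 20.8% in both arms, 10 centres, 31 or 32 patients per arm per centre, beta-distributed surgeon risks, 40,000 runs per setting. Type I error of the continuity-corrected chi-square, with the uncorrected centre-stratified Mantel-Haenszel test in brackets:

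| ICC | k = 1 | k = 2 | k = 4 |
|---|---|---|---|
| 0.005 | 5.6% (6.7%) | 4.8% (5.9%) | 4.3% (5.3%) |
| 0.01 | 7.4% (8.9%) | 5.5% (6.7%) | 4.8% (6.0%) |
| 0.02 | 10.8% (12.5%) | 7.0% (8.5%) | 5.2% (6.5%) |
| 0.03 | 13.8% (16.1%) | 8.8% (10.4%) | 6.0% (7.4%) |

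At an event risk of 16.7% the results lie within about half a percentage point of these. With no surgeon variation the corrected test rejects in about 4% of runs and the Mantel-Haenszel test in about 5%.

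**Overlap.** With the same surgeon in both arms in half of the centres (one surgeon per arm per centre), the corrected test gives 5.6% at ICC 0.01 and 6.9% at 0.02 (Mantel-Haenszel 6.9% and 8.5%). With the same surgeon in both arms everywhere, and a surgeon effect common to both techniques, the corrected test gives 3.0% to 4.1% and Mantel-Haenszel 4.9% to 5.2% for every ICC from 0 to 0.10.

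**The case against.** Four points can be made for the plan.

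- **Nothing fixes the nesting.** The article permits overlap and gives no surgeon numbers and no ICC. A reader might infer that the type I error exceeds 5% as a matter of course. The documents do not support that: with full overlap there is no inflation, and because the continuity correction starts the planned test near 4%, it stays below 5% in part of the assumed range (two surgeons at ICC 0.005; four at 0.005 and 0.01). This stands, and the point is therefore conditional.
- **The target of inference is a choice.** Patients are individually randomized, so for the question whether the arms differ as delivered by these particular surgeons, the planned test keeps its level. This is correct, but the article states its conclusion about the techniques in general, and an interval for that needs to include variation between surgeons.
- **The analysis plan is not shown.** It may add a surgeon model. That is possible, but the tests and the level of adjustment are stated here, and centre is the only level named.
- **A surgeon model is expensive as a gatekeeper.** A reader might infer that superiority should be claimed only if the surgeon model agrees. With one surgeon per arm per centre there are about 9 degrees of freedom. The planned difference over its standard error is 0.0832 / √[(0.208 × 0.792 + 0.1248 × 0.8752)/315] = 0.0832/0.0295 = 2.82. A t-test on 9 degrees of freedom then has about 71% power with no surgeon variation, 60% at ICC 0.01 and 51% at ICC 0.02, against the planned 80%. This stands and rules out such a condition.

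**Conclusion.** The concern holds in conditional form. The design makes it likely that surgeon is wholly or partly nested in arm, the named tests ignore surgeon, and adjustment for centre does not cure this. If surgeons are separate by technique and outcomes vary by surgeon, the 95% CI for a conclusion about the techniques is too narrow and the type I error can exceed 5%.

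For an ICC of 0.005 to 0.03 without overlap, the planned continuity-corrected test runs at about 5.5% to 14% with one surgeon per arm per centre, 5% to 9% with two and 4% to 6% with four. The uncorrected Mantel-Haenszel test runs at about 7% to 16%, 6% to 11% and 5% to 7%. The upper figures need one surgeon per arm in every centre and an ICC at the top of the range. The ICC, the surgeon numbers and the degree of overlap are assumptions, so the actual size for this trial cannot be stated from the documents.

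**What to change.** 1. Record the operating surgeon for every patient in the trial database.
2. Keep the stated primary test.
3. Pre-specify a sensitivity analysis of the 30-day composite: a logistic model with treatment and centre as fixed effects and surgeon as a random intercept, or surgeon-clustered variance, in either case with a small-sample correction.
4. Report its odds ratio and CI beside the primary result, together with the number of surgeons per arm and how many operated in both arms.
5. Word the conclusion cautiously if the two analyses disagree. Do not make the model a condition for claiming superiority.

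The cost is one data field, one extra model and a wider interval in the sensitivity analysis. The model corrects the precision only. It does not remove a systematic difference in skill between the two groups of surgeons, so the counts and overlap in step 4 are needed to interpret the result.

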### Surgical Technique

Surgical access to the heart will be gained through a median sternotomy in all of
the patients. In order to reduce the risk of bleeding and transfusions an
absorbable hemostat is used to sternal bone marrow and recovery of red blood
cells in all patients. Off-pump surgery will be performed with the use of heart
stabilizers. Patients will be heparinized with 250 IU/kg intravenously to
achieve activated clotting time >200s. The proximal anastomosis will be
performed according to protocol to be discussed with our advisor. The distal
anastomosis will be constructed with the help of mechanical stabilizers and
cardiac positioner. Intracoronary shunts will be used routinely. On-pump surgery
will be performed in normothermia, with the use of aortic cross-clamping and
cold cardioplegic arrest. Patients will be heparinized with 500 IU/kg to achieve
an activated clotting time >480 s. Heparin will be neutralized with 1 mg
protamine sulfate per 5000 IU given. During the trial, there will be no changes
in the 2 surgical techniques that followed a pre-established protocol.

### Data Storage, Follow-Up and Outcome Measures

All variables from the study will be stored online through a REDCap Web Platform
(http://www.project-redcap.org/).The REDCap is a secure web application for
building and managing online surveys and databases. REDCap can be used to
collect virtually any type of data, it is specifically geared to support data
capture for research studies. This will be done through national healthcare
card, address and telephone numbers. On the basis of the registers, it will be
collected copies of hospital records and death certificates during the follow-up
period. The neurocognitive tests will be planned in accordance with the
statement of consensus of assessment of neurobehavioral outcomes after cardiac
surgery^[22]^.

We will assess health-related quality of life using the World Health Organization
quality of life questionnaire^[23]^. Neurocognitive and quality of life tests will be carried
out at baseline and at 6 months postoperatively. No follow-up visits will be
planned; however, patients will be routinely seen by the referring cardiologist
1 and 6 months after the operation. Hospital records and death certificates will
be blinded for the allocated treatment and forwarded to 2 randomly selected
members of the adjudication committee, who will assess whether each of the
pre-specified outcomes had occurred. In case of disagreement, the 2 assessments
together with a copy of the record of the event will be sent to a third member,
who will have to select the most likely assessment.

